### Data collection methods

5.2

The authors were previously trained to collect data and perform the surgeries. All authors are qualified in photobiomodulation therapy. All data will be entered electronically. The participants’ files will be stored in numerical order in a safe place and accessible only to the authors of this study.

### Discontinuing intervention

5.3

The application of LEDs offers minimal risk, however, if during treatment, some participants report increased pain or display an infectious condition, measures such as the use of analgesics and/or antibiotics will be adopted according to clinical tolerance and individual assessment. These participants will be excluded from the study and will be followed up by the surgical team until resolution of the condition.

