**Methods::**

A randomized, double-blind, placebo-controlled clinical trial involving 38 adult participants, who meet the criteria of eligibility and agree to participate in the study. Before the surgeries are performed, the facial and mouth opening measures of all the participants will be taken. Immediately after the surgeries, participants will be randomized into 2 groups. In the LED group, participants will receive LED applications (intra oral with 660 nm, 12J and extraoral with 850 nm, 108J) in the immediate postoperative, first and second days after the surgical procedure. In the control group, the participants will be attended in the same way as in the LED group, however, the person in charge of the application will simulate the irradiation. Pain (EVA and NRS-101), postoperative edema, trismus, temperature, dysphagia, and hematoma will be evaluated after 1, 2, 5, and 7 days. The oral health impact profile (OHIP-14 Questionnaire) and anxiety analysis (Beck anxiety inventory -BAI) questionnaires will be applied preoperatively and 7 days after treatment. The appropriate statistical tests will be applied for each specific analysis in a significance level of 5%.

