### Sample calculation

2.3

A sample calculation based on the parameters of variability of the article of Eshghpour, Ahrari ^[13]^ based on the pain analysis of the participants on the 3rd postoperative day evaluated by a visual analog scale (VAS) was performed. Using a power of 80% and level of significance of 5%, a minimum sample size of 17 cases per group was obtained, making a total of 34 participants for the study. Winpepi software version 10.5 was used for this calculation. Considering a loss of 10%, based on the study that was used for the sample calculation, a loss of 2 participants per group should be predicted. Therefore, the total number of participants to be selected will be 38 individuals.

*Inclusion criteria*:Need of surgical removal of retained lower third molars;Agree to participate in the study after reading and signing the Informed Consent Term;Participants with indication for extraction of lower third molars (recurrent infections, bad position, and orthodontic indication) or professional written indication, healthy patients (negative medical history), systolic blood pressure lower than 140 mm Hg, and diastolic blood pressure lower than 90 mm Hg and heart rate values of 70 ± 20 beats/minute. The upper and lower central incisor teeth must be present.

*Exclusion criteria*:Systemic diseases, chronic pain or neurological and psychiatric disorders;Smokers;Using anti-inflammatories, analgesics or bisphosphonates in the last 15 days;Present active pericoronarite;Pregnant;Breastfeeding;Severe temporomandibular disorders;Photosensitivity history;Allergic to any drug used in the research (paracetamol, chlorhexidine 2%);Participants presenting radiolucent images associated with the teeth to be extracted;Participants who present any type of complication during surgery (hemorrhage, operative difficulty, time greater than 90 minutes of surgery), as these cases are not in the standard expected for third molar surgeries. In this case, the central action analgesic will be prescribed. These data will not be part of the statistical analysis but will be described and discussed.

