### Recruitment and randomization

2.4

Thirty-eight participants of both genders referred to the Faculty of Dentistry of UFRGS who need to perform the removal of lower third molars will be selected. Participants will be approached by means of an oral invitation to be conducted after verifying the eligibility criteria of the subject for the research.

To randomly distribute the subjects in the 2 experimental groups, a draw will be made with numbers. As the numbers are drawn, they will compose the experimental groups. Opaque envelopes will be identified with each number and inside it a sheet containing the information of the corresponding experimental group will be inserted according to the order obtained in the draw. The envelopes will be sealed and will remain sealed in numerical order in a safe place until the time of the surgeries. The drawing and preparation of the envelopes will be performed by a person who is not involved in the study.

Participants will be evaluated by the surgeon and when they meet all eligibility criteria previously described, they will be included in the study. All will be submitted to the same surgical protocol. Immediately after the surgeries, the researcher responsible for applying the LED will remove and open one envelope (without changing the numerical sequence of the other envelopes) and perform the indicated procedure.

The 38 participants will be allocated in the experimental groups as follows:

LED group (n = 19): Participants will receive 3 applications of intraoral LEDs with 660 nm and extraoral with 850 nm (Oncollux, Cosmedical, São Paulo, SP, Brazil) in the immediate postoperative, first and second days after the surgical procedure. The intraoral irradiation will be performed with a 6 red LED cluster and in the extraoral site a 36 infrared LED cluster will be used. The parameters of red/infrared LED are describe in Table 1.

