### Postoperative pain evaluation

3.5

In this project, we intend to apply 2 scales: the VAS and NRS-101. The VAS will be printed on the patient evaluation form and the subjects will be instructed by the evaluator to mark a point on the 10 cm line, indicating the intensity of their pain after 1.2, 5, and 7 days of the surgeries For the NRS-101 scale, the evaluators will ask participants to assign a number between 0 (no pain) and 100 (worst possible pain) that best represents the pain they are currently experiencing after 1, 2, 5, and 7 days of surgeries.

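### Section 5.3 removes randomised participants for increased pain or infection during treatment, so exclusion depends on the outcome that sized the trial

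*Protocol article*

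**What the plan says.** The abstract places allocation after surgery: "Immediately after the surgeries, participants will be randomized into 2 groups". Sections 2.4 and 3.4 agree, with the envelope opened once suturing is complete. Sessions are given "in the immediate postoperative, first and second days after the surgical procedure", that is, on days 0, 1 and 2.

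Section 5.3 then sets a rule for what may follow: "if during treatment, some participants report increased pain or display an infectious condition". Analgesics and/or antibiotics are given according to individual assessment, and "These participants will be excluded from the study and will be followed up by the surgical team until resolution of the condition". The only follow-up mentioned after exclusion is clinical.

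Pain is scored on the VAS and the NRS-101. For the latter, participants give the number "that best represents the pain they are currently experiencing after 1, 2, 5, and 7 days of surgeries". Pain also sized the trial: the calculation in Section 2.3 was "based on the pain analysis of the participants on the 3rd postoperative day evaluated by a visual analog scale (VAS) was performed". For attrition the same section says that "a loss of 2 participants per group should be predicted".

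Three other places also remove participants:
- Section 2.3 leaves operations with complications out of the statistical analysis.
- Section 3.2 says that the data of certain participants will be described but not analysed. Which participants it means is unclear.
- Section 5.1 excludes anyone who misses a scheduled session.

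No section states that all randomised participants are analysed.

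**The concern.** A participant can be removed because of the variable on which the arms are compared. Removal after allocation on the basis of pain selects on the outcome, and the participants left in each arm are no longer the groups that randomisation formed.

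The direction depends on the truth. If LED reduces pain, fewer LED participants meet the trigger, the controls lose more of their worst scores, and the observed difference shrinks. If LED increases pain or infection, the affected LED participants leave and the harm is under-reported.

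The wording adds to the problem. Increased pain has neither a threshold nor a reference point, and some pain is expected after this operation, so the rule could reach few participants or many. Nobody is named as the person who decides. If outcomes on days 5 and 7 are not collected after exclusion, no later analysis can recover them.

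**Working it through.** **1. The plan's own figure.** Section 2.3 gives 17 per group and a 10% loss allowance. 17 / (1 − 0.10) = 18.9, rounded up to 19 per group, or 38 in total. This agrees with the protocol. The 17 itself cannot be reproduced, because no difference or SD is stated.

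**2. Implied effect.** For a two-sided 5% t-test (sidedness is an assumption) with 17 per arm and 80% power, the standardised difference is d = 0.991. The normal approximation √(2/17) × (1.960 + 0.842) gives 0.96. With d = 0.991 and all 19 per arm kept, power is 84%.

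**3. Model of the rule (assumptions).** Pain is normal with SD 1 in both arms. A common cut-off c on a trigger score removes the worst share q of controls. The trigger score has correlation ρ with the analysed pain score and shows the same difference d between the arms. The documents give neither q nor ρ.

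Let λ(x) = φ(x)/Φ(x). The mean difference among those kept is

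d − ρ × [λ(c) − λ(c + d)],

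and the share of LED participants removed is 1 − Φ(c + d).

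| q (controls) | c | λ(c) | λ(c + d) | LED removed | Difference, ρ = 1 | Difference, ρ = 0.5 |
|---|---|---|---|---|---|---|
| 10% | 1.282 | 0.195 | 0.031 | 1% | 0.83 | 0.91 |
| 20% | 0.842 | 0.350 | 0.077 | 3% | 0.72 | 0.85 |
| 30% | 0.524 | 0.497 | 0.135 | 6.5% | 0.63 | 0.81 |

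Example for q = 10%, ρ = 1: 0.991 − (0.195 − 0.031) = 0.83.

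**4. Power**, by simulation (at least 40,000 trials, 19 randomised per arm, t-test on those kept):

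| q (controls) | ρ = 1 | ρ = 0.5 |
|---|---|---|
| 5% | about 80% | about 81% |
| 10% | 75% | 77% |
| 20% | 65% | 69–70% |
| 30% | 54% | 61% |

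**5. No true effect (d = 0).** With the same trigger in both arms, the two λ terms cancel, so there is no bias. The simulated type I error is 0.049 to 0.052.

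**6. Harm direction.** Assume that LED worsens pain by 0.5 SD, with ρ = 1. At q = 10/20/30% the visible worsening is 0.32/0.26/0.21 SD, and about 22/37/49% of LED participants are removed.

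**The case against.** The strongest reply is that this is a rule for complications and not a cut at a pain score. Section 5.3 describes the risk as minimal, ties the trigger to added medication, and confines it to the treatment period. Pain that rises after day 2 is not clearly covered, and even at 10% removal nine in ten controls stay. This part stands: a reader might infer that the comparison is made only among those who did well, and the text does not go that far.

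Other stronger readings also fail:
- **The 80% power is lost.** This depends on an unknown exclusion share. At 5% of controls removed, power is still about 80%, and the only loss figure in the protocol is 10%. Setting ρ = 1 is the upper end: the trigger falls on days 0 to 2, while the trial was sized on day 3.
- **The rule produces a false positive.** With no true effect and a common trigger it does not, and if LED works the bias runs towards no effect.
- **The unblinded operator drives the exclusions.** Section 3.4 says that the operator performs no evaluation and that the examiner is blinded. The fair point is that no decision-maker is named.
- **Infection is an effect of LED.** The documents give no basis for this; it is only a possibility that the trial should be able to detect.

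The attenuation is in original SD units. Truncation also shrinks the SD. At 30% and ρ = 1 the variances of those kept are about 0.49 and 0.78, so the standardised difference is 0.63 / √((0.49 + 0.78)/2) = 0.79, a fall of about 20% against 36 to 37% in raw units.

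One may also say that excluded from the study need not mean excluded from the analysis, or that a fuller plan may cover the matter. But Section 5.3 is an affirmative rule, after which only clinical follow-up is mentioned. The related rules in Sections 2.3 and 3.2 pair removal with non-analysis, although the surgical complications in Section 2.3 arise before the envelope is opened. A fuller plan would have to override the sentence in Section 5.3.

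**Conclusion.** The point holds. Section 5.3 prescribes an outcome-dependent exclusion after randomisation, and nothing in the protocol article reverses it. The damage is to the effect estimate, to power and to safety reporting; under a common trigger it is not to type I error.

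The direction follows from the rule, provided the trigger works alike in both arms. The size does not: it rests on an assumed exclusion share, an assumed correlation between trigger and analysed pain, normal scores and the implied 0.99 SD. Over 10 to 30% of controls removed, the understatement runs from about 0.08 SD (10%, correlation 0.5) to 0.36 SD (30%, correlation 1), and power lies between 77% and 54%. At 5% removed the loss of power against the stated 80% is negligible. These figures are an illustration and not a forecast.

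It should be corrected before the trial proceeds, because outcomes that were never collected cannot be restored at analysis.

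**What to change.** Reword Section 5.3 so that stopping the intervention and leaving the study are separate events. Participants with increased pain or infection receive whatever care the clinicians decide. They remain in the study, complete the blinded assessments already scheduled on days 1, 2, 5 and 7, and are analysed in the arm to which they were randomised. Report infection and additional analgesic or antibiotic use by arm. An analysis without these participants may be kept as a labelled sensitivity analysis.

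State in Section 3.13 that all randomised participants are analysed as allocated, and bring Sections 3.2 and 5.1 into line, including which participants the sentence in Section 3.2 refers to.

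The cost is a wording change plus completion of the scheduled study visits by these participants. The surgical team's follow-up until resolution does not replace those visits, since it is clinical care and not blinded outcome assessment.

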### Availability of data and materials

5.4

All information collected from the participants will be transcribed into a database replacing the individuals’ names with the registration number of the evaluation form. The datasets generated and analysed during the present study are available from the corresponding author at reasonable request. After the analysis of the data, volunteers will be invited to a meeting and the results will be shared and they will become public.
